**Figure 1 F1:**
[figure not shown]
Diagram showing Design of the Study.

### The intervention

#### Enhanced relapse prevention

The intervention was initially devised by one of the authors (RM) [17] and has been developed further for this study by the PI (FL) one of the grant holders (PK) and the trial therapist (LT). A detailed manual outlining the rationale and process of the intervention is given to all CCs and service users. This forms the basis of a collaborative intervention.

#### Training and supervision

The training takes place over six 2-hour long sessions, occurring approximately weekly. The training is offered in NHS accommodation at a time and location most convenient to the teams being trained. The training follows the six-session format of the intervention and the aim of each session is to ensure the CCs understand the rationale for the content of each session and feel able to work with service users to achieve the session aims. The training includes a mixture of didactic information-giving, group discussion, videoed role-play examples (using professional actors), and in-situ role play tasks.

Following the training, all CCs are offered weekly clinical supervision for three months during which time they are expected to offer the intervention to at least one service user. The supervision is offered in groups consisting of CCs from the same team. All of the training and supervision sessions are conducted by the trial therapist (LS). CCs are asked to give feedback on the training and supervision. At the end of the intervention with the first service user, they are asked to rate their perceived competency and confidence in offering the intervention. Each individual is also rated by the trial therapist at the same time point.

### Data collection and analysis

A breakdown of reasons for exclusion and reasons for withdrawal from the training, intervention and follow-up phases of the study will be provided (Figure 1). Table 1 shows the timeframe for the assessments and measures that are used with service users with Bipolar Disorder. All measures are completed at face to face interview expect where indicated otherwise. Interviews take place in the service users' home, or a suitable NHS site.

**Table 1 T1:** Schedule of Quantitative Assessments for Service Users

**Assessment**	**0 weeks (baseline)**	**12 weeks**	**24 weeks**	**36 weeks (by telephone)**	**48 weeks**
***Primary Outcome measures***					

Hamilton Rating Scale for Depression	+	+	+	+	+
Bech-Rafaelsen Mania Scale (MAS)	+	+	+	+	+
Current mental state coding (SCID-I)	+	-	-	-	-

***Secondary Outcome measures***					

LIFE scores for mania and depression for current week	+	+	+	+	+
Social and Occupational Functioning Assessment Scale (SOFAS)	+	+	+	-	+
Client Service Receipt Inventory (CSRI)	+	-	+	-	+

***Process measures***					

# Early Warning Signs Checklist (Mania and Depression)	+	+	+	-	+
# Coping strategies Checklist (Mania and Depression)	+	+	+	-	+
# Brief Illness Perception Questionnaire for Bipolar Disorder (modified IPQ)	+	+	+	-	+

***Potential confounds***					

Demographics	+	-	-	-	-
Clinical data*	+	+	+	-	+
Lifetime coding of mental illness (SCID-I)	+	-	-	-	-
SCID-II coding for Borderline and Antisocial Personality Assessment	+	-	-	-	-
Verona Service Satisfaction Scale (VSSS-EU)	+	-	-	-	+
Relationship Quality Rating	+	+	+	-	+

*Clinical data includes current medication, start and end dates of last episode and history of episodes over the previous 3 years.

# designed or significantly modified for this study

### Primary outcomes

The primary aims of the study are to assess the acceptability and feasibility of the trial design, and to estimate the effect size of the impact of the intervention on outcome.

#### Acceptability and feasibility

Recruitment, retention and attendance rates for CCs, service users, and relatives will be reported. Likert scale ratings of the quality of training and supervision and of CC competence and confidence in using ERP will be analysed. Barriers to carrying out the study at each stage will be identified and discussed and potential solutions identified.

Semi-structured in-depth interviews are conducted with a subsample of Care Coordinators and service users from each arm of the trial, and relatives involved in ERP. The aims are to: explore experiences of care coordinators of training and implementation of ERP within an NHS setting; to identify factors involved in the implementation and effectiveness of the ERP intervention for CC (at an individual, team and organisational level), service users and relatives or friends; to ascertain what TAU is for those with Bipolar disorder as received/provided by their care coordinators; and to explore the experiences of relatives/friends of service provision and their role in the management of Bipolar disorder.

A purposive maximum variation sampling strategy is deployed for each interview group and is an iterative process. Thus, on the basis of initial analysis, additional participants are selected who are thought to be able to fill-in, expand, or challenge previous data. At most 20 to 30 interviews will be conducted for each group although this may vary if data saturation is obtained, or if vagaries of data collection impede the attainment of theoretical saturation. Data are analysed using a grounded theory [18] approach. Following a constant comparative approach, an initial coding frame is complied, which is refined and elaborated in the light of incoming data and ongoing analysis. The results of the qualitative analysis will be reported elsewhere on completion of the trial.

#### Impact of the intervention on outcome

An estimate of the effect size of the intervention will be made from a comparison of time from baseline to recurrence of an episode of major depression, hypomania, mania, or mixed, satisfying DSM-IV criteria [19] following at least 8 weeks below this level for that pole. The number and percentage of patients satisfying criteria for a DSM-IV episode, broken down by type (major depression; mania type; other), will be reported for each treatment group and overall. The number and percentage of patients for whom information is imputed will also be reported. The intervals (in days) from baseline to recurrence (of any type) will be summarised by Kaplan-Meier curves (plotted up to 48 weeks). Cox proportional hazard models with robust variance estimators will be used to provide estimates of the hazard ratios and 95% confidence intervals.

The main analyses will be conducted on all patients from all teams (assigned to treatment groups (ERP and TAU) as randomised), applying the principle of intention to treat (ITT), as far as is practically possible, given any missing data. Sensitivity analyses based on a "per protocol" (PP) analysis will be conducted to examine robustness of the main results to departure from intended trial treatment. The sample of patients for the PP analyses is defined as the sample for the ITT analyses minus those patients who could not have received sufficient trial treatment due to CCs not attending at least 4 training sessions, or service users receiving less than 4 sessions of ERP. Given that the study is a feasibility study used in part to estimate the sample size for a larger study, effect sizes with 95% confidence intervals will be given weight rather than reliance on levels of statistical significance alone.

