### Design

ERP is a stratified cluster randomised controlled trial with extensive evaluation of the process as well as the outcome of the trial. CMHTs are randomly allocated to receive training and supervision in ERP or to continue to offer Treatment as Usual (TAU). The number of teams in each Trust is identified prior to randomisation. The variable for stratification is NHS Trust. This is to take into account different systems and approaches for working with Bipolar Disorder between Trusts and also any changes in guidelines for working with BD that may appear during the period of study. Teams are allocated numbers, which are then randomised electronically. Service users with BD from teams in both arms are assessed by researchers blind to allocation on a range of outcome measures for up to 48 weeks following the onset of treatment. All incidences of unblinding are recorded.

A cluster design is considered necessary because all members of a CMHT need to be able to understand and implement an individual relapse prevention plan for all service users. Although each service user has a named CC, other members of the team are closely involved in their care through out-of-hours cover, crisis management, co-working etc. Therefore any training aimed at modifying practice should be offered to teams rather than individuals. Data from service users with Bipolar Disorder who are within the same cluster i.e. seen by the same team, are not independent. Other variables, such as team set-up, previous team training, management style, etc. are likely to influence the outcome of the intervention. Failing to account for this clustering effect is may result in under-powered studies [15].

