There are a number of important limitations to the study that need to be addressed in future work. Firstly, this study is designed to assess the impact of clustering at the level of CMHT and to account for this in the statistical analysis of outcome. However, in reality the study has 2 levels of clustering: the CMHT and the Care Coordinator. Each Care Coordinator is asked to offer the ERP intervention to a minimum of 3 service users. It could be argued that data from service users who receive the intervention from the same Care Coordinator is likely to be correlated more highly than that from different Care Coordinators within the same team. However, due to the fact that the number of people within each cluster at the CC level would be likely to be very small i.e. 3, and the total sample would be insufficient to explore multiple level clustering, this will not be accounted for in the analysis.

Secondly, we have argued that a cluster design is required because ERP is essentially a team approach. Service users may need to be able to contact the CMHT at very short notice in response to increased recognition of important changes in their early signs of relapse. An effective and reliable response from the team is essential. For this reason, whichever CMHT staff member is currently on duty should be able to work with the ERP plan. In reality, we have recruited teams with a minimum of 4 CCs consenting to take part. This is for purely pragmatic reasons. In setting up the study, services felt unable to commit the time and resources for all staff to attend. Although the documentation regarding early signs monitoring and action plans is available in the service users notes, future work needs to address the best ways to disseminate information within and between mental health teams. It is possible that this limitation will reduce the effectiveness of the intervention.

Thirdly, due to the time constraints on the study, we are unable to recruit all service users prior to randomisation at each NHS Trust site. CCs make referrals throughout the study and generally offer ERP sequentially to one person at a time. Teams in TAU also make referrals throughout as more people who are eligible are identified. We are assessing and will report on whether or not this has led to a recruitment bias.

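### The per-protocol exclusions fall in practice only on the ERP arm and depend partly on sessions received after baseline, so the per-protocol hazard ratio cannot by itself show that the ITT result is robust

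*Protocol article*

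**What the plan says.** All of this is in the Protocol article, mostly under *Impact of the intervention on outcome*.

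- **Main analysis.** "The main analyses will be conducted on all patients from all teams", with patients kept in the group to which their team was randomised.
- **Per-protocol analysis.** It is a sensitivity analysis and "will be conducted to examine robustness of the main results to departure from intended trial treatment". Its sample is the ITT sample less patients judged unable to have had enough of the trial treatment, "due to CCs not attending at least 4 training sessions, or service users receiving less than 4 sessions of ERP".
- **Endpoint and clock.** The effect size comes from a "comparison of time from baseline to recurrence of an episode of major depression, hypomania, mania, or mixed". "The intervals (in days) from baseline to recurrence (of any type) will be summarised by Kaplan-Meier curves" up to 48 weeks, and Cox models with robust variance give the HR.
- **Who gets training and sessions.** Under *Design*, teams are randomised either to training and supervision in ERP or to continuing usual treatment.
- **Timing of delivery.** The *Discussion* describes six one-hour sessions and says that care coordinators (CCs) "generally offer ERP sequentially to one person at a time". No calendar time to session 4 is given.

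**The concern.** Two features of the rule combine.

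1. **It is one-sided.** A TAU patient has no trained CC and no ERP sessions to fall short of, and no matching TAU exclusion is defined. The per-protocol comparison therefore sets a selected ERP group against an unselected TAU group.
2. **The session criterion looks forward from the time origin.** The clock starts at baseline, but whether a patient reaches four sessions is known only later. An ERP patient who recurs or disengages before session 4 may never reach it, and is then removed together with the event. A comparable TAU patient who recurs in the same week stays and counts.

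At stake is how the sensitivity analysis is read. A per-protocol HR further below 1 than the ITT HR could be taken as confirmation, or as the effect to expect with adequate delivery. A shift in that direction can arise with no effect at all. The same section gives weight to effect sizes and intervals because they feed the sample size of a larger trial.

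**Working it through.** The article states no sample size, event count or per-protocol figure, so there is nothing to reproduce. The check asks what the rule does to the HR when ERP has no effect.

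**Inputs from the article:** recurrence of about 50% at one year (*Background*); 48 weeks of follow-up; clock from baseline; Cox HR.

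**Assumed, because the article does not give them:** a constant hazard; the week *s* at which session 4 falls; the share *q* of ERP patients recurring before week *s* who then miss session 4.

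**Step 1, hazard.** λ = ln 2 / 52 = 0.01333 per week. Recurrence by 48 weeks: 1 − exp(−48λ) = 0.473.

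**Step 2, who is at risk of removal.** Recurrence before week *s* is F(s) = 1 − exp(−λs). F(8) = 0.101 and F(12) = 0.148.

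**Step 3, apparent 48-week recurrence in the reduced ERP arm.** It is (0.473 − q·F(s)) / (1 − q·F(s)), while TAU stays at 0.473.
- s = 8, q = 1: (0.473 − 0.101) / (1 − 0.101) = 0.41
- s = 12, q = 1: (0.473 − 0.148) / (1 − 0.148) = 0.38

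**Step 4, Cox HR by simulation.** 2,000,000 patients per arm, true HR 1.00. Only ERP patients who recur before week *s* and then miss session 4 are dropped.

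| Session 4 at week | q = 25% | q = 50% | q = 100% |
|---|---|---|---|
| 4 | 0.97 | 0.95 | 0.89 |
| 8 | 0.95 | 0.90 | 0.79 |
| 12 | 0.93 | 0.85 | 0.70 |
| 24 | 0.87 | 0.74 | 0.45 |

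The share of ERP patients dropped runs from 1.3% (week 4, 25%) to 27.4% (week 24, 100%).

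**Step 5, fewer early events.** Entry requires four weeks free of an episode, and a recurrence requires at least eight weeks below threshold for that pole. Some same-pole events in the first weeks may therefore not count. With no countable event in weeks 0 to 4:

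| Session 4 at week | q = 50% | q = 100% |
|---|---|---|
| 8 | 0.94 | 0.88 |
| 12 | 0.89 | 0.78 |
| 24 | 0.76 | 0.50 |

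**Step 6, other reasons for missing sessions.**
- 20% of ERP patients dropped for reasons unrelated to outcome: HR 1.00.
- Two risk classes with a hazard ratio of 2 between them, low-risk patients missing more (30% against 10%): HR 1.045.
- The same classes, high-risk patients missing more: HR 0.957.

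**Step 7, a symmetric rule.** Requiring patients in both arms to be recurrence-free at the session-4 week, and restarting the clock there, gave HRs of 0.998 to 1.003 in every Step 4 scenario. The artefact in that table thus comes from removing early events in one arm only.

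**The case against.** A reader might infer four stronger things, and the article supports none of them.

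- **That the per-protocol analysis must produce a false ERP benefit.** The sign and size depend on why sessions are missed, and the article gives neither rates nor reasons. Step 6 shows that no bias, or a small bias against ERP, is possible. The rule sets no deadline for session 4, so a patient who recurs may still complete four sessions later and stay in. A share of 100% is therefore an extreme. Sequential delivery does not prove a long wait after baseline either: *Design* describes assessment for up to 48 weeks from the onset of treatment, which may point to a short gap.
- **That both exclusion rules use conduct after baseline.** Training attendance is staff conduct. Training precedes delivery, and referrals continue throughout the study, so it can precede a given patient's baseline. Only the session rule clearly looks forward. The training rule still has no TAU counterpart.
- **That the rule, taken literally, removes the whole TAU arm.** The clause governing it concerns patients who cannot have had enough of the trial treatment. That makes sense only for patients allocated to ERP.
- **That the trial's effect estimate is compromised.** The main analysis is ITT, the per-protocol analysis is labelled a sensitivity analysis, and this is a feasibility study without a power calculation.

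These points limit the certainty and the size of the concern. They do not restore the stated purpose: an analysis whose bias turns on unknown reasons for non-attendance cannot show that another result is robust.

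**Conclusion.** The concern holds in a limited form. The exclusions work only in the ERP arm, and the session criterion depends on what happens after the time origin. The per-protocol HR is therefore open to selection and immortal-time bias, probably towards ERP, and cannot alone support the ITT result.

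With session 4 at week 8 or 12 and a quarter to all of early recurrers missing it, the artefact is of the order of 0.95 down to 0.70 under no effect. It is smaller if early events cannot count, and absent if missed sessions are unrelated to outcome. These figures rest on a constant hazard and on assumed values of *s* and *q*, so they illustrate the mechanism and do not predict this trial's result. What needs correcting is the role given to the per-protocol analysis; the ITT analysis stands as planned.

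**What to change.** 1. State that the per-protocol exclusions apply to the ERP arm only. Label the result descriptive, and withdraw its use as evidence of robustness.
2. To address departures from treatment, add one or both of the following.
   - **Complier average causal effect for 48-week recurrence.** Use randomisation as the instrument, define a complier as a patient with at least four ERP sessions, and use team-clustered standard errors. With no ERP in the TAU arm, the estimate is the ITT risk difference divided by the proportion of ERP patients with at least four sessions. If allocation has no effect, the numerator is zero in expectation, whatever the reasons for missed sessions. State the assumption that allocation has no effect in patients with fewer than four sessions. It is doubtful here, because the article presents ERP as a team-level approach.
   - **Landmark analysis.** Fix the landmark week in advance and apply the same recurrence-free requirement in both arms. This removes the early-event artefact but not selection by prognosis among those who complete four sessions.

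A rank-preserving structural failure time model is not required.

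The cost is a change of analysis wording. *Acceptability and feasibility* already commits to reporting attendance, so no new data should be needed. The price is wider intervals and the assumptions just stated.

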### Secondary outcomes

The effect of the intervention and the clustering design on secondary outcome and process measures will be assessed over 12 months. Secondary outcomes include symptom severity, social and occupational functioning, and cost of services received in each arm of the trial. Specific hypotheses linked to these are that (1) ERP will improve outcome compared to TAU by reducing the severity of symptoms; (2) ERP will improve outcome compared to TAU by improving social and occupational functioning; (3) there will be no difference in the overall cost of services received between those receiving ERP and those receiving TAU. Whilst it is recognised that ERP may initially require additional contact with the CC, following the intervention, service users who have received ERP will be better able to manage their own mood changes and are less likely to experience a relapse or require an admission to hospital.

Severity ratings of overall symptom levels based on the LIFE-II (Longitudinal Interval Follow-up Evaluation) will be obtained at weekly intervals post-baseline to 48 weeks. These will be averaged over intervals of four weeks, separately for depression and mania, and analysed by multilevel modelling to allow for the repeated measures and cluster design. Multilevel models will also be used to compare social and occupational functioning and cost of services, between groups.

### Process measures

Measures will be used to try to understand the process by which any changes occur. Process measures include recognition of early warning signs of relapse, use of coping strategies, and beliefs about mental health problems. Specific hypotheses linked to these measures are: (1) ERP will improve outcome compared to TAU by increasing the frequency of monitoring for early warning signs, and the number of signs identified in the early phase of relapse. (2) ERP will improve outcome compared to TAU by increasing the number and perceived effectiveness of appropriate coping strategies for managing early warning signs of relapse (Coping Strategy Checklist (modified from Lam & Wong 1997 [20]); (2) ERP will have a positive impact on service users beliefs about their mental health problems (Brief Illness Perception Questionnaire for Bipolar Disorder (modified from the IPQ Weinman et al 1996 [21]). Multilevel models allowing for repeated measures and cluster design will be used to compare monitoring and recognition of early warning signs, use of coping strategies and beliefs about mental health problems between the groups.

### Potential confounds

A number of potential confounds have been identified on the basis of previous work in this area including number of previous episodes [22,23], amount of social support [24] and use of medication [25]. These are assessed and will be controlled for in the analyses.

## Discussion

This study is essential in providing information necessary to the planning and execution of a definitive evaluation of the clinical effectiveness of relapse prevention approaches for Bipolar Disorder in the NHS.

We have devised an enhanced form of a relapse prevention approach that has already been shown to reduce relapse rates for mania. The enhancements are designed to: improve the effectiveness of the intervention at reducing rates of relapse into depression; make the intervention more widely available by tailoring it specifically to be used by CCs currently working in the NHS (rather than requiring referral to specialist services); streamline the intervention by identifying the key elements that can be offered in six, one-hour sessions; involve a friend or relative which is likely to increase the effectiveness of the intervention and make it more acceptable to service users. This intervention is highly consistent with the psychosocial components of treatment recommended by the recent NICE Clinical Guidelines for Bipolar Disorder [9].

We have designed the feasibility study to provide as much detailed and accurate information as possible. The inclusion criteria for staff and for service users are as wide as possible to increase generalisability. The manual and all training materials are designed to a high standard and quality for wider dissemination. Detailed feedback is sought on the training and supervision. The service user assessments include well standardised, valid and reliable measures of the key outcome variables, along with extensive qualitative interviews to explore the experiences of participants in depth. The research team meet on a regular basis to discuss and log barriers faced in conducting the research and ideas for how these could be avoided/overcome in future work. A detailed picture is obtained about how the intervention is used in practice.

There are a number of important limitations to the study that need to be addressed in future work. Firstly, this study is designed to assess the impact of clustering at the level of CMHT and to account for this in the statistical analysis of outcome. However, in reality the study has 2 levels of clustering: the CMHT and the Care Coordinator. Each Care Coordinator is asked to offer the ERP intervention to a minimum of 3 service users. It could be argued that data from service users who receive the intervention from the same Care Coordinator is likely to be correlated more highly than that from different Care Coordinators within the same team. However, due to the fact that the number of people within each cluster at the CC level would be likely to be very small i.e. 3, and the total sample would be insufficient to explore multiple level clustering, this will not be accounted for in the analysis.

Secondly, we have argued that a cluster design is required because ERP is essentially a team approach. Service users may need to be able to contact the CMHT at very short notice in response to increased recognition of important changes in their early signs of relapse. An effective and reliable response from the team is essential. For this reason, whichever CMHT staff member is currently on duty should be able to work with the ERP plan. In reality, we have recruited teams with a minimum of 4 CCs consenting to take part. This is for purely pragmatic reasons. In setting up the study, services felt unable to commit the time and resources for all staff to attend. Although the documentation regarding early signs monitoring and action plans is available in the service users notes, future work needs to address the best ways to disseminate information within and between mental health teams. It is possible that this limitation will reduce the effectiveness of the intervention.

Thirdly, due to the time constraints on the study, we are unable to recruit all service users prior to randomisation at each NHS Trust site. CCs make referrals throughout the study and generally offer ERP sequentially to one person at a time. Teams in TAU also make referrals throughout as more people who are eligible are identified. We are assessing and will report on whether or not this has led to a recruitment bias.

Fourthly, we are not able to assess fidelity to the intervention for all service users. The trial therapist makes a rating of adherence to the manual for the service users who are offered the intervention during the period of supervision. However, after completing the first intervention, CCs are offering ERP to service users outside of supervision. There is no assessment of fidelity for these interventions.

These limitations are clearly important and need to be addressed in future work. However, despite these, the results from this study are essential in progressing research and clinical innovation in this area. If we are able to show that it is feasible to train CCs in the NHS to offer ERP for people with Bipolar Disorder, it will be possible to design a large scale definitive trial to evaluate the effectiveness of the intervention on relapse rates. Such an intervention has the potential to offer service users a way of increasing control over their mood disorder and ultimately improving their quality of life and that of their relatives and friends.
